## Abstract

**Introduction:**

Generalized anxiety disorder (GAD) is the most common type of anxiety disorders. GAD usually occurs in adolescence or early adulthood, and the prevalence of GAD is higher among college-enrolled young adults than in the general adult population. However, there is a lack of evidence regarding the effectiveness of acupuncture in the treatment of GAD. This study’s objective is to evaluate the efficacy of acupuncture in the treatment of GAD in college students and its stability.

**Methods:**

A total of 142 subjects will be recruited for the randomized controlled trial (RCT) of current undergraduate and graduate students with GAD and will be randomized into treatment and control groups. The treatment group will receive conventional acupuncture, while the control group will receive sham acupuncture using Streitberger needles. Both groups will be administered 8 acupuncture treatment (2 times per week for 4 weeks). The follow-up duration will be 2 months. The Hamilton Anxiety Scale (HAMA) will be used as the primary outcome of the study to measure the severity of anxiety disorder. The secondary outcomes of this study will be included the Pittsburgh Sleep Quality Index (PSQI) and Self-rating anxiety Scale (SAS). The study will also evaluate the success of blinding and the safety.

**Discussions:**

Findings of this RCT will help evaluate the efficacy of acupuncture treatment for GAD in college students, potentially promoting it as an alternative treatment option. The protocol was registered at clinicaltrials.gov (Identifier: ChiCTR2400080688)

## 1. Introduction

Generalized anxiety disorder (GAD) is the most common type of anxiety disorder, a chronic psychiatric condition characterized by persistent tension and accompanied by autonomic hyperfunction and increased vigilance. GAD usually occurs in adolescence or early adulthood, and the prevalence of GAD is higher among college-enrolled young adults than in the general adult population [1]. WHO World Mental Health Surveys International College Student Project surveyed about 14,000 university students in eight countries and found that the prevalence of GAD was about 18%, second only to major depression [2]. The survey results of 621 university psychological counseling centers in 2018 showed that anxiety was the main reason for students to visit campus psychological health counseling centers [3]. The high prevalence of GAD among college students may reflect the transition from adolescence to adulthood, which is characterized by entering a more independent living environment, increasing personal decision-making responsibilities, and having non family living partners [3]. Anxiety disorders during college have been associated with smoking, sleep problems, and even low academic performance [4]. Meanwhile, there is shown that the presence of anxiety disorders in early adulthood increases the risk of other neurological disorders later in life [5].

The main treatments currently used for GAD include pharmacologic and non-pharmacologic treatments [6]. Pharmacotherapy has some shortcomings while achieving certain therapeutic effects, such as specific adverse reactions, long-term oral easy to lead to drug resistance and addictive, and easy to discontinue the drug withdrawal reaction, which leads to poor adherence to the therapy [7]. Non-pharmacological therapies include psychotherapy, cognitive-behavioral therapy, relaxation therapy, etc., which are affected by many factors and have unstable efficacy, making it difficult for patients to adhere to the treatment for a long time [7]. Therefore, the search for a compliant, safe, and effective treatment is a research trend.

Acupuncture is one of the current therapies for the treatment of GAD [8,9]. As early as the Western *Jin* Dynasty, acupoints for the treatment of mood disorders, such as the *Neiguan* (PC6), were recorded. The "Thirteen Ghost Acupoints" of the *Tang* Dynasty are still highly valued in the treatment of various mental disorders. Clinical trials in recent years have also shown a role for acupuncture in the treatment of GAD [10]. However, there is a study showing that acupuncture has no therapeutic effect on GAD [11]. Therefore, the present study is conducted to evaluate the efficacy and stability of acupuncture in the treatment of GAD in college students with significant health economics.

## 2. Methods

### 2.1 Study design overview

This is a single-center, prospective, sham acupuncture controlled, randomized controlled trial. Patients will receive 2 courses of acupuncture + conventional medication or sham acupuncture + conventional medication after randomization. The schedule of enrollment, intervention, and assessment is shown in Fig 1. Each patient will be treated for 4 weeks, with a late follow-up of 2 months; this includes baseline assessment (week 0), end of treatment period II (week 4), end of 1 month of follow-up, and end of 2 months of follow-up (Fig 2). The reporting of this study protocol is based on the Consolidated Standards of Reporting Trials (CONSORT) checklist [12] and the Standards of Reporting Trials and Revised Standards for Reporting Interventions in Clinical Trials of Acupuncture (STRICTA) checklist [13].

**Fig 1 pone.0316804.g001:**
[figure not shown]
Schedule of enrollment, intervention, and assessment.

**Fig 2 pone.0316804.g002:**
[figure not shown]
Study flow chart.

### 2.2 Participants: Recruitment and selection

Patients with GAD will be enrolled in the study. The diagnostic criteria based on the Diagnostic and Statistical Manual of Mental Disorders will be used [14]. The following inclusion criteria will be used: current undergraduate and graduate students, those aged 18–30 years; 7≤HAMA total score≤21. Exclusion Criteria: (1) severe organic lesions or current treatments that would make acupuncture unsuitable; (2) anxiety disorders caused by depression or by other psychiatric disorders; (3) inability to cooperate; (4) pregnant and lactating women; (5) participated in other clinical studies in the past 3 months; (6) intolerance to acupuncture treatment.

A total of 142 GAD subjects will be recruited from the acupuncture clinic of the Third Affiliated Hospital of Zhejiang Chinese Medical University through poster advertising. The evaluation of the baseline for the subjects will be conducted within 1 week prior to the first intervention. All subjects will receive written informed consent forms.

All researchers will receive specialized training on the purpose, content, and treatment strategies for quality control. All acupuncturists have at least 5 years of undergraduate education and a certificate of TCM practice. The Monitoring Committee of the Third Affiliated Hospital of Zhejiang Chinese Medical University will monitor the safety of this study and review the results.

This study is approved by the Ethics Committee of the Third Affiliated Hospital of Zhejiang Chinese Medical University (approval number: ZSLL-KY-2023-027-01) and registered at the Chinese Clinical Trial Registry. The relevant information of the study will be provided to all subjects in detail, and they will be given sufficient time to consider whether to participate in the study. If the subjects agree to participate in the study, they will sign an informed consent form. The results of the study will be published at an online medical journal.

### 2.3 Sample size

Following Cohen’s statistical power analysis guidelines, [15] we determine that a medium effect size (d = 0.50) is appropriate for this study, given the absence of preliminary data or prior research that could offer specific effect size estimates. In situations lacking pilot data, selecting a medium effect size is recommended to balance statistical power requirements and resource constraints, while ensuring the ability to detect clinically meaningful differences. Since our primary outcome measure (HAMA score) is a continuous variable that will be compared between groups using means, we applied Cohen’s recommendations for t-tests between independent means. According to these guidelines, 64 subjects per group are required to detect a medium effect size (d = 0.50), with type-I error (α) = 0.05 and power (1-β) = 0.80. Accounting for an anticipated 10% dropout rate, we will recruit 71 subjects per group, resulting in a total sample size of 142 participants. This sample size calculation ensures adequate statistical power to detect clinically meaningful differences between groups while accounting for potential attrition.

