### 2.10 Statistical analyses

The data are analyzed using IBM SPSS (V.25.0), and all statistical tests are taken as two-sided tests. The statistical significance is set at P<0.05. In terms of descriptive statistics, continuous variables will be expressed as mean ± standard deviation, while categorical variables will be expressed as frequencies and percentages.

In terms of comparisons of measurements, as the HAMA, PSQI, and SAS scores are ordinal, non-parametric tests are prioritized for analyzing group differences. For between-group comparisons of HAMA, PSQI, and SAS scores, Mann-Whitney U test will be used; for within-group (pre- and post-test) comparisons, Wilcoxon signed-rank test will be applied. For categorical variables, Chi-square or Fisher’s exact tests will be used as appropriate.

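### The sample size is built on a t-test of mean HAMA, but the analysis section plans a Mann-Whitney U test on HAMA as an ordinal score, so the stated 80% power is for a test that is not planned

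*Protocol article*

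**What the plan says.** Section 2.3 (Sample size) describes the primary outcome and its comparison as follows: "Since our primary outcome measure (HAMA score) is a continuous variable that will be compared between groups using means". From this it concludes: "we applied Cohen’s recommendations for t-tests between independent means". The inputs are a conventional effect size ("a medium effect size (d = 0.50) is appropriate for this study") and the error rates ("with type-I error (α) = 0.05 and power (1-β) = 0.80"). They lead to 64 evaluable patients per group, raised to 71 per group and 142 in total for 10% dropout.

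Section 2.10 (Statistical analyses) takes the other view of the same score: "as the HAMA, PSQI, and SAS scores are ordinal, non-parametric tests are prioritized for analyzing group differences". It then names the test: "For between-group comparisons of HAMA, PSQI, and SAS scores, Mann-Whitney U test will be used". It also states that "all statistical tests are taken as two-sided tests". It names no t-test, linear model or other formal comparison of mean HAMA. Means with standard deviations appear only as the descriptive summary for continuous variables.

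**The concern.** The two sections disagree on what kind of variable HAMA is and on which test compares the groups. This is not detail left to a fuller document. Both sections make positive statements about the same comparison, and an analysis plan could follow only one of them.

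Two things are at stake:

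- **Power.** The 80% was derived for a test of means. It carries over to a rank test only approximately, and how closely depends on the shape of the HAMA distribution.
- **The primary result.** The design effect is a standardised difference in means, while the Mann-Whitney test compares ranks. With both approaches in the protocol, either could later be presented as the pre-specified one. If they fell on opposite sides of P = 0.05, the article would not say which decides.

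**Working it through.** **Inputs.** From section 2.3: d = 0.50, α = 0.05, power 0.80, 64 evaluable per group, 10% dropout, 71 recruited per group. From section 2.10: two-sided testing, Mann-Whitney U for HAMA. The article gives no HAMA standard deviation, difference in points or distribution, so every Mann-Whitney figure below rests on an assumed shape.

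**1. Reproduce the stated figure.** For a two-sided t-test (noncentral t) with d = 0.50, α = 0.05 and power 0.80, the exact n is 63.77 per group, which rounds up to 64. Power at 64 per group is 0.801. The stated 64 is therefore the t-test figure. Dropout: 64 / 0.9 = 71.1; the stated 71 leaves 71 × 0.9 = 63.9 evaluable, which is close enough.

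**2. Power of the planned test under the same normal shift.** The asymptotic relative efficiency of Mann-Whitney to the t-test under normality is 3/π = 0.955.

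- Effective n: 64 × 0.955 = 61.1 per group, giving power 0.783.
- Simulation of N(0,1) against N(0.5,1), 20,000 replicates, 64 per group: 0.776 to 0.782 across runs.
- Scores rounded to whole HAMA points, with an assumed SD of 4 to 6: 0.781 to 0.787.

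All of these round to about 0.78 or 0.79.

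**3. Sample size for 80% power with the rank test (normal shift).**

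- By relative efficiency: 63.77 / 0.955 = 66.8, so 67 evaluable; 67 / 0.9 = 74.4, so 75 recruited per group.
- By Noether's formula: P(X<Y) = Φ(0.5/√2) = 0.638; total N = (1.960 + 0.842)² / [12 × 0.25 × (0.638 − 0.5)²] = 137.1 with unrounded inputs, or 68.5 per group, so 69 evaluable; 69 / 0.9 = 76.7, so 77 recruited per group.

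The shortfall under normality is thus 3 to 5 evaluable patients per group. Put another way, 64 per group gives the rank test 80% power at d = 0.50 × √(66.8/64) = 0.51 instead of 0.50.

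**4. Dependence on shape.** Shift of 0.5 SD, 64 per group. The simulated t-test stays at about 0.80 for the uniform and gamma shapes.

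| Assumed shape | Mann-Whitney power |
|---|---|
| Lower-bound efficiency (0.864) | 0.74 |
| Uniform (flat) | 0.75 to 0.76 |
| Normal | about 0.78 |
| Gamma, shape 4 (skewed) | 0.85 |

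The rank test loses a little power for flat or normal data and gains for skewed data.

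**The case against.** The strongest reply is that the contradiction has little numerical consequence. A change of about 2 percentage points, or from d = 0.50 to 0.51, is well inside the uncertainty of an effect size chosen by convention without pilot data. If all 71 recruited per group were evaluable, simulated Mann-Whitney power under normality would be about 0.82. A bounded sum score may well be skewed after treatment, and the rank test would then do better than the t-test. Mann-Whitney is a valid primary test, and choosing it does not inflate the type I error. All of this stands, and it limits the point to a correction of moderate weight.

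A reader might infer that the trial is underpowered and must recruit about 75 to 77 per group. The article does not support this. Those figures hold only for a normal shift, and the distribution of HAMA is not given.

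A reader might also infer that the trial cannot show a difference in mean HAMA at all. That goes too far. If HAMA is summarised as mean and standard deviation, as section 2.10 provides for continuous variables, a mean difference and its interval can be derived from the group summaries and numbers. The absence of a named effect estimate is also something an unseen analysis plan may supply, so it is not in itself an error.

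One could argue that section 2.10 only gives priority to non-parametric tests and so leaves room for a t-test. The sentence after it removes most of that room by fixing Mann-Whitney for HAMA.

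**Conclusion.** The point holds as an inconsistency that should be fixed. Sections 2.3 and 2.10 cannot both describe the primary comparison, and the stated 80% at 64 evaluable per group is the power of a t-test that section 2.10 does not plan. Under a normal shift of d = 0.50 the planned test has about 0.78. Across plausible shapes the figure runs from about 0.75 to 0.85, so the effect on power is small and its sign uncertain. The case for correction rests mainly on the primary analysis being stated in two ways, and only secondarily on power.

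**What to change.** Before unblinding, name one primary analysis of HAMA and make both sections agree with it. There are two routes.

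1. **Compare means.** Report the between-group difference in HAMA points with a 95% confidence interval, with Mann-Whitney as a sensitivity analysis. Adjusting for the baseline HAMA already collected is preferable. That is an improvement beyond section 2.3, which assumes an unadjusted comparison, and should be presented as such. The sample-size text can then stay.
2. **Keep Mann-Whitney.** Restate the power in section 2.3 as about 0.78 at 64 evaluable per group under a normal shift of d = 0.50, say that it depends on the distribution, and report a shift estimate (for example Hodges-Lehmann) with its confidence interval.

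In either case, describe HAMA as continuous or as ordinal, but the same way in both sections. The cost is wording in two sections, with no added patients. Under the second route the stated power becomes slightly less favourable.

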### 2.4 Blinding

We will implement blinding for patients, outcome evaluators, and statisticians. The treatment group will be needled at relevant acupoints and *de qi*, while the control group will be needled without breaking the skin and no *de qi*. In the process of treatment, acupuncturists will carry two different types of needles to avoid patients guessing their grouping. In accordance with previous studies using sham acupuncture in this field, [16,17] an independent researcher will evaluate the success of patient blinding using a validated questionnaire. Within 30 minutes after their final treatment, participants will be asked to choose one of three options: "Needled," "Not Needled," or "I Don’t Know". The patients’ responses will indicate whether they are successfully blinded to their treatment allocation. The Bang’s blinding index will be calculated based on the results of this questionnaire, thereby determining the overall effectiveness of our patient blinding protocol.

### 2.5 Randomization and allocation concealment

The randomization will be performed using permuted block randomization with varying block sizes (4, 6, and 8) to ensure balanced group sizes while maintaining allocation unpredictability. The randomization sequence will be generated by an independent statistician using SAS 9.4 software. The generated allocations will be sealed in sequentially numbered, opaque envelopes by an independent research coordinator. Each envelope will contain the group assignment, a unique participant identifier, and date and signature lines for documentation. These envelopes will be stored securely and opened sequentially only after participant eligibility is confirmed and informed consent is obtained. The research coordinator will then open the envelope and inform the acupuncturist of the treatment assignment prior to the participant’s first treatment session, with the date and time of envelope opening being recorded and signed by both the research coordinator and the treating acupuncturist. This process ensures both balanced group sizes and unpredictable allocation while preventing selection bias through proper concealment.

### 2.6 Intervention

(1) The treatment group

During the study period, patients will receive 2 courses of free acupuncture treatment. Treatment will begin on the day patients are randomized into groups. The treatment group will use *Hua Tuo* disposable acupuncture needles (0.25×40 mm, Suzhou Medical Supplies Factory Co., Ltd, Suzhou, China). Patients in the treatment group will choose acupoints including, *Baihui* (GV20), *Yintang* (GV29), *Shenmen* (HT7), *Danzhong* (CV17), PC6, *Taichong* (LR3). The specific anatomical locations of the aforementioned acupoints are detailed in Table 1. GV20, GV29, and CV17 will be punctured 0.3–0.8 inch flat, HT7, PC6, and LR3 will be punctured 0.3–1 inch straight. And leave the needles for 30 minutes after *de qi*. Patients will receive 8 acupuncture treatments (2 times per week for 4 weeks).

**Table 1 pone.0316804.t001:** Location of the acupoints.

Acupoints	Anatomical Locations
GV20	On the head, 5 *cun* straight up from the center of the front hairline
GV29	On the head, in the depression between the inner ends of the two eyebrows
CV17	On the chest, transverse to the fourth intercostal space, on the anterior midline
HT7	In the anterior region of the wrist, at the ulnar end of the distal transverse line of the palmar side of the wrist, at the radial margin of the ulnar flexor tendon
PC6	In the anterior region of the forearm, 2 *cun* above the transverse stripe on the distal part of the palmar side of the wrist, between the tendon of the palmaris longus and the tendon of the flexor carpi radialis muscle
LR3	The first and second metatarsal bones on the dorsum of the foot

(2) The control group

Sham acupuncture via Streitberger needles will be used in the control group. With references to similar studies involving sham acupuncture, the selected sham points are the non-acupoints, away from meridians, located on the back, under the spinous processes of the third thoracic vertebra to the seventh thoracic vertebra, and 2 *cun* away from the posterior midline [17]. A total of 8 points on both sides of the back will be subjected to "acupuncture", and the duration of needle retention and the number of treatments will be the same as those in the treatment group. It is worth noting that the use the above non-acupoints in a prone position for the control group is also an attempt to enhance patient blinding.

### 2.7 Outcome measures

#### 2.7.1 Primary outcome

The primary outcome is the evaluation of patient anxiety using the Hamilton Anxiety Scale (HAMA) at weeks 4, at the end of the month 1 of follow-up, and at the end of the months 2 of follow-up. The HAMA total score provides a good response to the severity of anxiety symptoms, and the scale includes 14 items, all of which are rated on a 5-point scale from 0–4. A HAMA *<*7 represents no anxiety; HAMA ≥7 represents possible anxiety; HAMA ≥14 represents definite anxiety; HAMA ≥21 represents significant anxiety; and HAMA ≥29 represents severe anxiety.

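### HAMA is primary at three unranked visits with no stated success rule, while the sample size covers one comparison, so the stated 5% error and 80% power do not both hold

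*Protocol article*

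**What the plan says.** Section 2.7.1 of the protocol article sets the primary outcome as HAMA "at weeks 4, at the end of the month 1 of follow-up, and at the end of the months 2 of follow-up". The three visits stand side by side. Neither the abstract nor the design overview (section 2.1) singles one out.

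Section 2.3 rests on one comparison of means: "we applied Cohen’s recommendations for t-tests between independent means". It concludes that "64 subjects per group are required to detect a medium effect size (d = 0.50") and completes the calculation "with type-I error (α) = 0.05 and power (1-β) = 0.80". It then adds: "Accounting for an anticipated 10% dropout rate, we will recruit 71 subjects per group", which gives 142 in total. It does not say which visit this comparison concerns.

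Section 2.10 states that "all statistical tests are taken as two-sided tests" and that "The statistical significance is set at P<0.05". On the method it says: "For between-group comparisons of HAMA, PSQI, and SAS scores, Mann-Whitney U test will be used". It names no longitudinal model or summary over visits.

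**The concern.** The sample size provides for one primary test, but the outcome definition yields three. The Mann-Whitney test takes one score per patient, so the natural reading is one test per visit, each against 0.05. The article does not use the words 'at each visit', so this is an inference, but no other route from three visits to one test is described.

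With no deciding visit and no rule for combining the three results, the meaning of a positive trial could be settled after the results are known. A difference at one visit could be reported as efficacy, or its absence at another as failure. The article itself cites evidence both for and against acupuncture in GAD and intends the result to guide practice, so the claim should rest on a rule fixed in advance.

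**Working it through.** **Inputs from the article.** Three primary visits (section 2.7.1); two-sided 0.05 (section 2.10); d = 0.50, alpha 0.05, power 0.80, 64 evaluable and 71 recruited per group (section 2.3).

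**Assumption.** The article gives no correlation between the HAMA test statistics at different visits. A common correlation ρ is taken from 0 to 0.9, with 0.5 to 0.8 as the working range.

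**Step 1: reproduce the plan's figure.** For one two-sided t-test with d = 0.50, the noncentrality is 0.50 × √(n/2). The exact power is 0.795 at n = 63 and 0.801 at n = 64, so 64 per group is right for one test. For dropout, 64 / 0.9 = 71.1, against the stated 71. The difference is immaterial here.

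**Step 2: any one visit counts as success.** If the tests were independent, the chance of at least one false positive would be 1 − 0.95³ = 0.1426. For correlated tests it is P(at least one |Z| > 1.96) for three standard normal statistics with common correlation ρ:

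| ρ | Familywise error | Multiple of 5% |
|---|---|---|
| 0 | 14.3% | 2.9 |
| 0.5 | 12.5% | 2.5 |
| 0.7 | 10.9% | 2.2 |
| 0.8 | 9.8% | 2.0 |
| 0.9 | 8.4% | 1.7 |

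A correlation that decays with time (AR(1)) gives slightly more: 12.9% at 0.5 and 10.3% at 0.8. Simulated Mann-Whitney tests on rounded scores with 64 per group agree: 12.0%, 11.1% and 9.4% at ρ = 0.5, 0.7 and 0.8.

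**Step 3: all three visits must be significant.** Under the null at every visit, the chance of three significant results is about 0.3% at ρ = 0.5 and 1.4% at ρ = 0.8, so error is not inflated. For power, each statistic has mean 0.50 × √(64/2) = 2.83 (normal approximation), assuming d = 0.50 holds unchanged at all three visits:

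| ρ | Power, all three significant |
|---|---|
| 0.5 | 62% |
| 0.6 | 64% |
| 0.7 | 67% |
| 0.8 | 70% |

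If the effect fades during follow-up, power is lower still.

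**Step 4: Bonferroni over the three visits.** The level is 0.05 / 3 = 0.0167. The t-test with 64 per group then has power 0.656 at any given visit. Reaching 80% per visit takes 86 evaluable per group (power 0.804; 85 gives 0.799), or 86 / 0.9 = 95.6, rounded up to 96 recruited. These are powers for a given visit. The chance of success at one or more visits is higher if the effect is present at several.

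**The case against.** The strongest reply is that the document states no any-visit rule. A reader might infer that the false-positive rate simply is about twice 5%. The text does not support that as a fact: it holds only if one significant visit suffices, and under an all-three rule the error is about 0.3% to 1.4%. The multiple also depends on a correlation the article does not give. Both objections stand, so the error figures are conditional and shown as a range.

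A reader might also infer that the 5% level is wrong for some of the individual tests. It is not. Each test at 0.05 keeps its own 5% error, and what is left uncontrolled is the rate across the three.

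Nor was the sample size computed for week 4: section 2.3 names no visit. The stated aims mention efficacy and stability together and give no testing order.

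Finally, this is a journal article, and a multiplicity method or testing order may sit in an analysis plan that is not shown. Its absence here is therefore not the point. What remains is something the article itself fixes: three unranked primary visits beside a sample size for one comparison. The primary time point belongs to the definition of the primary outcome, and the article states it as three.

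**Conclusion.** The point holds as a mismatch between sections 2.3, 2.7.1 and 2.10. The success rule is undefined, and either simple reading breaks a stated figure. If any visit suffices, familywise error is 9.8% to 12.5% at ρ = 0.8 to 0.5 (8.4% to 14.3% over 0.9 to 0) in place of 5%. If all three are required, power is about 62% to 70% in place of 80%. A Bonferroni correction would restore the error rate but leave about 66% power at any given visit.

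The results rest on visit-by-visit testing, which is the natural reading but not stated. They also rest on assumed between-visit correlations and, for power, on d = 0.50 persisting to month 2. The calculation of 64 per group is itself correct for one test. Because the point concerns how the primary conclusion is reached, it should be settled before unblinded data are seen.

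**What to change.** In section 2.7.1, name one visit as the single primary endpoint, and in section 2.10 test it at two-sided 0.05. The calculation of 64 per group and 142 in total then applies to that visit, and section 2.3 should say so. Week 4, the end of treatment, is a sensible choice, though this is a proposal and not something the article implies. Make the other two HAMA visits key secondary endpoints in fixed order, month 1 and then month 2, each tested at 0.05 only if the one before it is significant. This holds the familywise error over the three visits at 5% and lets the follow-up visits speak to stability.

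A different pre-specified single visit, or one pre-specified longitudinal contrast, would also resolve the point.

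The cost is wording in three sections, with no extra patients or visits. The downside is that no confirmatory follow-up claim can be made if the primary visit is negative.
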